### Criteria for discontinuing or modifying allocated interventions {11b}

Drop-out or early discontinuation indicates a patient who has signed an IC, was eligible and enrolled with at least one trial-specific assessment, and discontinued the clinical trial for any reason before the end of the trial, as defined in the trial protocol. Reasons for drop-out/discontinuation are defined as withdrawal upon participant´s request; investigator-initiated discontinuation (e.g., medical reasons); lost to follow-up: cessation of participation without notice or action by the patient; sponsor-initiated discontinuation. Reasons for sponsor-initiated discontinuation may be insufficient regression of CoNV or prolonged healing phase after CXL so that the timeframe to the pKPL can not be respected.

### Strategies to improve adherence to interventions {11c}

Participants will receive a detailed, written treatment plan from clinical or study nurses explaining how and when to take their medications to encourage and monitor adherence. Participants who cannot apply eye drops themselves will receive treatment from the clinical nurses during the hospital stay. Attrition bias will be minimized by sending timely reminders of follow-up appointments to patients and arranging substitutes for any missed visits.

In general, corneal transplant patients have a high adherence to treatment as they usually already have a long ophthalmologic history and are eager to improve the outcome of their transplant. The allocation rate of 5:4 was chosen to allow a (slightly) higher number of patients in the intervention group since CXL is a minimally invasive and safe approach expected to reduce the risk of transplant rejection and discover even rare complications.

### Relevant concomitant care permitted or prohibited during the trial {11 d}

There are no restrictions on local and systemic therapies for patients receiving keratoplasty, including immunosuppressants. Topical steroids will be used postoperatively, with monthly reduction, topical antibiotics for two weeks, and cycloplegia during the first week. Systemic carboanhydrase inhibitors will reduce pressure on the transplant, and topical steroids and antibiotics are used and tapered as needed. Patients with corneal pathology due to herpesvirus will be treated according to guidelines using broad antivirals.

### Provisions for post-trial care {30}

All patients will be followed up for 2 years after corneal transplantation. After the end of the trial, further treatment will be based on the respective clinical findings and solely determined by the responsible ophthalmologist. For all trial subjects enrolled travel accident insurance is provided.

### Outcomes {12}

Primary endpoint: The primary endpoint is the time to the first corneal endothelial graft rejection episode within 24 months after transplantation.

Secondary endpoints: Secondary endpoints are overall functional graft survival rate, rejection-related graft failure rate, regression of pathological corneal vessels after CXL (after 1st and eventually 2nd), number of CXL needed for successful regression > 50% of CONV, recurrence of CoNV after CXL and after transplantation, visual acuity (using ETDRS charts; assessment before CXL, before transplantation and 3, 6, 12, 18, and 24 months after transplantation). Additional secondary endpoints are the vision-related quality of life measured using the National Eye Institute Visual Function Questionnaire (NEI-VFQ25) and the safety, organizational, and administrative aspects of the trial [19, 20].

The anterior segment and the cornea will be examined by slit-lamp biomicroscopy and photo-documented. The corneal thickness will be documented by pachymetry. Visual acuity will be measured by ETDRS charts, and vision-related quality of life will be measured using the NEI-VFQ25 [19, 20].

### Participant timeline {13}

The planned participant timeline over the whole trial duration is shown in Table 1.

**Table 1 Tab1:** Timeline over the trial duration

First patient first visit (FPFV):	Quarter (Q) IV 2023
Last patient first visit (LPFV):	Q III 2025
Last patient last visit (LPLV):	Q III 2027
End of trial:	Q IV 2027
Final study report:	Q III 2028

The planned participant timeline of visits with procedures per visit and overview of the trial as a flowchart is shown in Table 2 and Fig. 1.

**Table 2 Tab2:** Participant timeline of visits with procedures

Visits	Screening	Baseline	Control after CXL^a^	Repeat study intervention^b^	Control after the second CXL	Transplantation^c^	FU				
Trial points	Week −14 to −10	Week −10 to −8	Week −8 to −6	Week −6 to −4	Week −4 to −2	D 0	Week 12±2 wk	Week 24±2 wk	Week 48±2 wk	Week 72±2 wk	Week 96±2 wk
Eligibility and history	X										
Informed consent	X										
In-/exclusion criteria	X										
Demographics	X										
Medical history	X										
Slit lamp exam	X	X	X		X		X	X	X	X	X
Standardized digital photo		X	X		X		X	X	X	X	X
Laser-FlareCell-Meter^d^		X					X	X	X	X	X
Corneal tomography	X	X	X		X		X	X	X	X	X
SL-OCT	X	X	X		X		X	X	X	X	X
Visual acuity	X	X	X		X		X	X	X	X	X
Concomitant medication	X	X	X		X		X	X	X	X	X
Randomization^e^	X										
Vision-related quality of life		X					X	X	X	X	X
CXL (intervention group only)		X		X							
Transplantation						X					
AE review and evaluation			X	X	X		X	X	X	X	X
Corneal endothelial count							X	X	X	X	X
Macula OCT^f^	X						X	X	X	X	X

*AE *Adverse event, *CXL *Corneal crosslinking, *FU *Follow-up, *EOT *End of trial, *SL-OCT *Slit lamp optical coherence tomography

^a^Two weeks after the first CXL, ^b^when regression of corneal neovascularization is < 50%, repeat CXL 4 weeks after first CXL, ^c^depending on availability of the graft and randomization, transplantation will take place between 8 and 10 weeks after baseline visit, ^d^optional (if available), ^e^after obtaining IC and completion of screening, ^f^if deemed necessary by the investigator

**Fig. 1 Fig1:**
[figure not shown]
Flowchart of the trial

### Sample size {14}

Sample size calculation is based on the primary endpoint, time from surgery to the first graft rejection episode, comparing the intervention and control groups using the log-rank test. The expected rejection rate in the control group was estimated using rates given in previously published studies [6, 21]. An overall 2-year rejection rate of 50% was assumed for the control group. The study was powered to detect a reduction in the 2-year rejection rate from 50 to 25% (hazard ratio 0.42) with 80% power at a significance level of 0.05 (assuming exponential survival curves and accrual of 22 months, with a subsequent follow-up period of at least 24 months). An allocation rate of 5:4 and continuous loss-to-follow-up cumulating to 20% at 2 years was accounted for, yielding a total sample size of 110 (intervention group: *n* = 61, control group: *n* = 49). Calculations were performed using SAS 9.4 (Proc Power).

### Recruitment {15}

Participants will be recruited among patients visiting the outpatient clinic or from the corneal transplantation waiting lists. Patients will receive a detailed explanation of the risks and benefits of the trial to ensure that they fully understand the specifics of the study. Then they will be asked to provide a signed IC form voluntarily. The organizers will try to reduce the loss of participants by reminding them of their appointments and rescheduling if needed.

### Assignment of interventions: allocation

#### Sequence generation {16a}

After signed IC, patients are randomly assigned to CXL (intervention group) or no CXL (control group) using the 24-7 Internet online randomization tool ALEA Clinical (FormsVision BV, Abcoude, NL). Randomization is stratified by the center and surgeon. A statistician, independent of the trial team, generated the randomization list using permuted blocks of varying sizes and uploaded it in ALEA. The study will compare the effects of CXL versus no CXL before corneal transplantation in high-risk patients with CoNV. The participants will be assigned to either group by chance, using a 5:4 ratio and a web-based service that ensures fair and unbiased allocation.

#### Concealment mechanism {16b}

Randomization is implemented by central 24-7 Internet randomisation service ALEA. Complete blinding is not possible (see {17a}). The ALEA service is accessed via a validated password website to ensure concealment.

#### Implementation {16c}

The study physician of the respective participating center will enroll eligible participants and randomize them via ALEA. Independent randomization administrators implement and manage the trial in ALEA and set system roles and access rights. Therefore, the allocation sequence is not accessible by investigators managing or assessing the study participants and the randomization result is unpredictable. The study physicians who decide whether a repetition of CXL is necessary are not the same as the surgeons.

### Assignment of interventions: blinding

#### Who will be blinded {17a}

This exploratory trial does not involve a sham CXL procedure, so concealing patients’ group assignment to surgeons is impossible. The clinical signs of treatment or no treatment should be easily identifiable. In case of successful preconditioning, there would be vessel regression, ghost vessels, and maybe even a small regression of corneal opacification. However, to minimize the risk of performance and detection bias, we will blind the surgeons and examiners of physician-reported outcomes and endpoints as much as possible. This means that the surgeon will not be the one to decide whether CoNV regressed sufficiently and if additional reducing treatment is required. Graders from the Cologne Ophthalmological Reading and Image Analysis Center (CORIC) will independently confirm the diagnosis of rejection episodes and graft failure and quantify CoNV changes.

#### Procedure for unblinding if needed {17b}

N/A. No blinding is planned (see above). Thus, there is no procedure for unblinding.

### Data collection and management

#### Plans for assessment and collection of outcomes {18a}

Administrative trial project management, data management, monitoring, and safety management are done by the Clinical Trials Center Cologne (ZKS). Potential patients will be pre-selected when encountered during clinical routine or by viewing the corneal transplantation waiting lists by the study physicians. After screening assessments are completed, inclusion and exclusion criteria will be validated. If all inclusion criteria are met and no exclusion criteria are present, consent for study participation can be obtained, and randomization can be performed.

At the baseline visit, a slit lamp examination and photo documentation and LaserFlareCellMeter (if available), corneal tomography, and Anterior Segment Optical Coherence Tomography (AS-OCT) measurements will be performed. In addition, visual acuity and vision-related quality of life will be assessed. Concomitant medication will be documented. Postoperatively, follow-up assessments will be performed at 3, 6, 12, 18, and 24 months for all subjects (postoperative visits at these time points are standard care). A slit lamp examination, concomitant medication, Adverse Events (AE), and photo documentation, as well as LaserFlareCellMeter (if available), corneal tomography, AS-OCT, and corneal endothelial cell count measurements will be performed. In addition, visual acuity and vision-related quality of life will be assessed.

The Principal Investigators will oversee and coordinate the collection, entry, and protection of data in the trial. The trial staff will collect trial-specific data using designated source documents and follow standard Good Clinical Practice (GCP) procedures to ensure accurate and consistent data collection. Any corrections made to source documentation must be documented and leave the original entries legible and signed or initialed with the correction date. A trackable audit trail is required if electronic patient files are used as source documents. All trial data must be verifiable to the source documentation and kept in a locked facility at the clinical site. Source documents include IC Forms, laboratory results, lists of adverse events and concomitant medication, NEI-VFQ-25, and documentation of existing conditions [19, 20]. Medical records will be archived according to local regulations. The Principal Investigators or their designees will document all relevant trial data in electronic case report forms (eCRFs), which will be reviewed by the clinical team for accuracy and completeness. The Principal Investigators may authorize trial staff members to sign the eCRFs to confirm data accuracy, and they will perform the final sign-off after follow-up visits.

Serious Adverse Events and Device Deficiencies must be entered in eCRF within two Business Days at the latest.

Previously determined staff ophthalmologists will decide whether CoNV sufficiently regressed following the first study intervention. Later, these data will also be centrally analyzed by graders of the CORIC and will be employed to diagnose rejection episodes and graft failure.

#### Plans to promote participant retention and complete follow-up {18b}

The distinguishing intervention between the two study arms (CXL) will be performed after trial entry. All trial participants will be monitored closely by the study team. PKPL will be the same for both groups. Follow-up is usually excellent after transplant surgery with low loss-to-follow-up rates. These patients have a long medical/ ophthalmological history and generally only participate in clinical trials if they are highly motivated. Our patients attend regular follow-up visits, especially outpatient clinics anyway. We do not foresee any difficulties in completing the evaluation. Attrition bias will be minimized by sending timely reminders of follow-up appointments to patients and arranging substitutes for any missed visits. Patients do not need to adhere to any other specific tasks.

### Data management {19}

Trial-specific data will be collected by the clinical trial staff using designated source documents. Standard GCP procedures will be followed to ensure accurate, reliable, and consistent data collection. Data will be handled pseudonymously.

The allocation sequence will be concealed from the investigators managing or assessing the study participants. After the allocation, trial participants, care providers, and outcome assessors will remain blinded throughout the trial as far as possible, except for the surgery.

The following demographic data will be collected upon inclusion: sex, age, visual acuity, intraocular pressure, study eye, uni-/bilaterality of the disease, genesis of neovascularization, duration of neovascularization, once or repeated CXL, percentage of reduction of neovascularization, fine needle diathermy, other relevant medical history, HLA type.

The CTCC will supply the IT infrastructure and data management staff. The trial database will be developed and validated before data entry based on standard operating procedures at the CTCC. The data management system is based on commercial trial software and stores the data in a database. All changes made to the data are documented in an audit trail. The trial software has a user and role concept that can be adjusted on a trial-specific basis. The database is integrated into a general IT infrastructure and safety concept with a firewall and backup system. The data are backed up daily. After completion and cleaning of data, the database is locked, and the data is exported for statistical analysis.

The clinical trial data will be entered online at the trial sites via the Internet. Plausibility checks are run during data entry, thereby detecting any discrepancies immediately. The CTCC Data Management will conduct further checks for completeness and plausibility and clarify questions with the trial sites electronically via the trial software. The trial site must answer these electronic queries without unreasonable delay. Further details will be specified in the data management plan. A guidance document and web-based training for data entry in the eCRF will be provided to the trial sites.

### Confidentiality {27}

All investigational materials and collected data will be pseudonymized using unique alphanumerical codes for each trial participant, and all applicable provisions of the data protection legislation will be followed. As part of the IC process, potential trial participants will be informed about the requirement to agree to handling pseudonymized data under applicable legislation to be eligible to participate in the trial. Patients who disagree with the data handling described in the IC form will not be enrolled in the trial. Patients will be referred to exclusively by their participant numbers. Clinical information, IC, and eCRFs will be stored closed off and protected against outside influence.

The sponsor (University of Cologne) is responsible for data processing. The sponsor representative is the Coordinating investigator.

### Plans for collection, laboratory evaluation, and storage of biological specimens for genetic or molecular analysis in this trial/future use {33}

The ophthalmologic pathology department will routinely evaluate all corneal specimens obtained during surgery. Additionally, tissue may be stored, e.g., in the blood bank of Cologne University Medical Faculty (using a separate consent form). So far, there is no study-specific storage planned. In case of any changes to the study plan, renewed ethical approval is required.

Sufficient regression of CoNV after 1st CXL and only after 2nd CXL	Regression of CoNV > 50% (intervention arm only)	Value (yes/no)	Proportion	After 1st CXL and after 2nd CXL
Recurrence of CoNV	Recurrence (after sufficient regression was reached; intervention arm only)	Value (yes/no)	Proportion	After CXL (until transplantation) and after transplantation (within 24 months)
Visual acuity (BCVA)	ETDRS charts (transformed to logMAR)	Value	Mean	Prior to CXL, prior to transplantation, and 3, 6, 12, 18, and 24 months after transplantation
Vision-related quality of life	Overall score of NEI-VFQ25	Value	Mean	Prior to CXL, prior to transplantation, and 3, 6, 12, 18, and 24 months after transplantation
Infections	Active infectious keratitis or corneal ulceration	Value (yes/no)	Proportion	Within 24 months
Delayed wound healing	Delayed wound healing: corneal epithelium not closed (delay) or closed (no delay)	Value (yes/no)	Proportion	Within 24 months after transplantation
Graft dehiscence	Graft dehiscence characterized by leakage of aqueous humor	Value (yes/no)	Proportion	Within 24 months after transplantation

Survival analysis techniques will analyze primary and key secondary endpoints, allowing all patients to contribute information for however long they were followed up. The calculation of the scales of the NEI-VFQ follows the respective manual; missing values will be handled as described therein [19, 20].

The safety analysis includes calculating and comparing specified complication rates (see secondary endpoints), adverse events, and device deficiencies. Furthermore, descriptive methods are used to assess the homogeneity of the treatment groups. Analyses will be done using SAS (SAS Institute Inc., Cary, NC, USA) or IBM SPSS Statistics (IBM, Armonk, NY, USA).

Subgroup analyses will be done based on age at transplantation, sex, pretransplantation degree of CoNV, number of previous grafts, and presence of systemic immunosuppression.

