### Intervention description {11a}

pKPL replaces all layers of the diseased central cornea with an allogeneic healthy graft from a deceased donor. pKPL will be performed as a standard full-thickness penetrating procedure, and the graft (individualized size between 6.5 and 8.25 mm in diameter) will be secured with at least 16 interrupted (or double running star-shaped) 10-0 nylon sutures.

CXL is a corneal treatment involving riboflavin and irradiating the cornea with UV-A light. An accelerated protocol is used, which involves higher illumination intensity (9 mW/cm^2^) and shorter UV-A irradiation time (10 min) [18]. A shield protects the limbus during the procedure to prevent damage to the limbal stem cells as we plan to irradiate the complete cornea. CXL will be performed in the intervention group to stabilize the recipient cornea and to reduce CoNV 8 to 10 weeks before pKPL. The control group will undergo pKPL without prior CXL. CXL can be repeated once at least 14 days before transplantation if CoNV is not completely regressed.

In case of residual CoNV on the day of transplantation, fine needle diathermy will be used in the intervention group. It involves coagulating blood vessels using a monopolar cautery unit and a bent needle. In the control group, no fine needle diathermy will be performed.

Postoperatively, all patients will be treated with topical corticosteroids and antibiotics, and a systemic carboanhydrase inhibitor will be given to reduce intraocular pressure on the transplant.

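### Tables 2 and 3 do not match: no NEI-VFQ25 is scheduled between Baseline and week 12 after surgery, and CoNV recurrence up to transplantation is only partly observable from the scheduled photos

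*Protocol article*

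**What the plan says.** Table 3 (Statistical methods for primary and secondary outcomes {20a}) defines the recurrence endpoint as "Recurrence (after sufficient regression was reached; intervention arm only"), a yes/no value reported as a proportion, with the time points "After CXL (until transplantation) and after transplantation (within 24 months"). For the NEI-VFQ25 overall score, and in the same words for visual acuity, the time points are "Prior to CXL, prior to transplantation, and 3, 6, 12, 18, and 24 months after transplantation".

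Table 2 (Participant timeline {13}) sets out which procedures belong to which visit. The row "Standardized digital photo" is marked at Baseline, at both post-CXL control visits and at the five follow-up visits. The row "Vision-related quality of life" is marked at Baseline and at the five follow-up visits only. In the transplantation column only the operation is marked. The narrative schedule in Plans for assessment and collection of outcomes {18a} also places quality of life at baseline and at the postoperative visits only.

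Intervention description {11a} adds an event on the day of surgery: "In case of residual CoNV on the day of transplantation, fine needle diathermy will be used in the intervention group".

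**The concern.** Two named secondary endpoints have time points that the visit schedule does not fully serve.

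For quality of life, the value between CXL and graft is the only one that could show what CXL itself does before the transplant changes everything else. Unless it is collected before the operation, it cannot be recovered.

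For recurrence, a patient counts only once sufficient regression has been documented, so scoring needs a later look at the same eye. If part of the window up to surgery has no scheduled image, a recurrence there cannot enter the centrally read data, yet the eye stays in the denominator. The reported proportion would then make regression look more durable than it was.

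**Working it through.** The plan states no figure to reproduce. The check sets the Table 2 rows against the Table 3 time points.

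| Table 2 visit | Week | Photo | NEI-VFQ25 | Visual acuity |
|---|---|---|---|---|
| Screening | −14 to −10 | – | – | X |
| Baseline (first CXL) | −10 to −8 | X | X | X |
| Control after CXL | −8 to −6 | X | – | X |
| Repeat CXL | −6 to −4 | – | – | – |
| Second control visit | −4 to −2 | X | – | X |
| Transplantation | 0 | – | – | – |
| Follow-up | 12, 24, 48, 72, 96 (each ±2) | X | X | X |

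**NEI-VFQ25.** Nothing is marked between Baseline and week 12.
- Shortest gap: 8 + (12 − 2) = 18 weeks. Longest gap: 10 + (12 + 2) = 24 weeks.
- Intervention arm: Baseline is the visit of the first CXL, so it supplies the pre-CXL value. The separate pre-transplant value has no scheduled assessment.
- Control arm: Baseline is a pre-transplant value, but it lies 8 to 10 weeks before surgery.
- Visual acuity has the same Table 3 time points and is marked at both control visits. The omission is therefore specific to the quality-of-life row.

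**Recurrence until transplantation.** The first control visit comes "Two weeks after the first CXL"; the later one is headed "Control after the second CXL".
- Eye that passes 50% regression only after the second CXL: regression is established at week −4 to −2, which is its last pre-operative photo. The 2 to 4 weeks to surgery have no scheduled photo, and the next is 10 to 14 weeks after surgery.
- Eye that passes 50% after one CXL and attends the second control visit: one later photo exists, at week −4 to −2. The last 2 to 4 weeks are again without a photo.
- Eye that passes 50% after one CXL and does not attend the second control visit: the last pre-operative photo is at week −8 to −6, so 6 to 8 weeks are without a photo.
- The total interval between photos around surgery is 2 + 10 = 12 to 4 + 14 = 18 weeks with the second control visit, and 6 + 10 = 16 to 8 + 14 = 22 weeks without it.

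**Direction of the error.** Let N be the eyes with sufficient regression and R those that truly recur before surgery. The scheduled photos can show at most the recurrences present at a later photo, say R′ ≤ R. The reported R′/N therefore cannot exceed R/N through this mechanism, and it falls short whenever a recurrence lies in an unphotographed stretch. The size of the shortfall cannot be calculated, because the article gives no expected rate of regression or recurrence.

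**After transplantation.** In the intervention arm, diathermy may remove vessels on the day of surgery, after the last scheduled photo. The week 12 photo is thus compared with an image 12 to 22 weeks older that precedes the diathermy.

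**The case against.** Three stronger conclusions are tempting, and the document supports none of them.

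- *A reader might infer that no recurrence before surgery can be seen in any of the 61 planned intervention patients.* That would need the second control visit to be confined to re-treated eyes, and CXL to be repeated only below 50% regression. No footnote confines the visit; only its column heading suggests it. Intervention description {11a} allows a repeat whenever regression is incomplete, whereas the Table 2 footnote sets the 50% limit. Under the former wording, an eye with more than 50% but incomplete regression can be re-treated and photographed again. The two statements of the trigger must be reconciled; this point takes no side between them.
- *A reader might infer that nobody examines the vessels before the operation.* The diathermy decision requires a judgement of residual vessels on that day. Data management {19} lists diathermy and the percentage reduction among the items collected, and Table 3 does not say that recurrence must be scored from a photo. What is missing is a scheduled, standardized image that the central reading center could grade.
- *A reader might infer that pre-transplant quality of life is missing for all 110 patients.* In the control arm the Baseline score is itself pre-transplant.

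It can also be said that these are secondary endpoints of an exploratory trial. No between-arm test uses recurrence before surgery, and the frequency table described in the analysis text covers recurrence after transplantation only. This stands and limits the weight of the point. The article also condenses a longer protocol. However, the mismatch lies between two tables printed in the article, and the narrative schedule sides with Table 2, so it is not detail left to another document.

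**Conclusion.** The point holds as a mismatch between Tables 2 and 3. Followed as printed, the schedule yields no NEI-VFQ25 score between CXL and graft in the intervention arm, and in the control arm only a Baseline score 8 to 10 weeks before surgery. Recurrence until transplantation is only partly observable from scheduled photos. At least the last 2 weeks before surgery are uncovered for every eye, up to 8 weeks if single-CXL eyes skip the second control visit, and eyes that respond only to the second CXL have no later pre-operative photo at all. The bias runs towards durable regression, and its size is unknown.

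This assumes that the visit windows are kept and that recurrence is graded mainly from standardized photos, in line with the reading center's task of quantifying CoNV changes. If the unscheduled judgement on the day of surgery were recorded and used as an outcome, the recurrence part would weaken; the quality-of-life part would not. The primary endpoint is unaffected.

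**What to change.** Reconcile the two tables.

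- In Table 2, add to the existing pre-operative admission the NEI-VFQ25 in both arms and a standardized photo, taken before any diathermy and read by the reading center with the others.
- State that the second control visit applies to all intervention-arm patients.
- Score recurrence until transplantation by comparing the pre-operative photo with the photo at which more than 50% regression was reached.
- Interpret recurrence after transplantation together with the recorded use of diathermy. The pre-operative photo does not show the vessels left after diathermy, so it is not by itself a clean reference.

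If nothing is added, delete the pre-transplant NEI-VFQ25 time point from Table 3 and end the pre-transplant recurrence window at the last control visit.

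The cost is one short questionnaire and one photo per patient, at an admission that takes place anyway and with readers already in the trial, plus a small eCRF amendment. If single-CXL patients were not expected at the second control visit, they would have that visit in addition. Patients already operated on cannot supply the missing values, so an early change keeps more of the data.
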